**Fig. 2 Fig2:**
[figure not shown]
Study flowchart

The primary objective is to develop a clinical screening tool for identifying older women with back pain who are likely to have VF. The output will be a simple clinical checklist of self-reported data and data from the physical examination which will produce a binary assessment of (1) yes—this person needs a spinal radiograph, or (2) no radiograph needed. The primary evaluative measure will be the accuracy of the Vfrac tool as represented by the sensitivity and specificity of > 80%.

### Study participant selection

General practices will be recruited from Bristol (9) and Stoke-on-Trent (16) areas. Practices will be recruited after an open call in the order they express an interest in the study until the number of participants target is reached at each site. The following entry criteria will be used for participants:

Inclusion: participant is willing and able to give informed consent for participation in the study, female, over 65 years and with self-reported back pain (via baseline questionnaire) in the previous 4 months.

Exclusion: male, 65 years or under, no self-reported back pain (via baseline questionnaire) in the previous 4 months, has already had a full spinal X-ray in the previous 4 months or considered unsuitable to take part by their GP (e.g. cognitive impairment, near end of life or recently bereaved).

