## Background and rationale

Osteoporosis is estimated to affect 200 million women worldwide [1]. Osteoporotic fractures are strongly associated with morbidity, especially in terms of pain and disability: out of the people who have had a fracture, 42% have chronic pain and 33% of these describe the pain as severe or unbearable [2]. People who are hospitalised after a vertebral fracture (VF) have a higher mortality rate following fracture than those hospitalised after a hip fracture [3]. Unlike mortality following a hip fracture, mortality after a VF rises progressively after the event [3]. However, unlike hip fractures, most VFs do not require hospitalisation. Furthermore, the socioeconomic burden of VF is not as well defined as that of hip fractures, in part because the epidemiology of VFs is less well established as there is no universally accepted definition.

Only 25% of VFs result from falls, with the majority caused by daily activities such as bending forwards, climbing stairs or lifting objects [4]. People with VFs have a reduced health-related quality of life that is not solely a result of confounding by age, nor can it be fully explained by the presence of pain [5]. VF in older people has an effect on everyday activities such as reducing their ability to get in and out of a car, lift objects from the floor, walk a few blocks, climb up and down steps, reach or extend their arms above shoulder level, prepare meals and do the shopping [6]. VFs can also deprive people of their social support because their physical and functional capabilities have been limited [7]. The presence of VFs increases the risk of subsequent fractures, especially further vertebral or hip fractures [8], although there are medications available to reduce this risk [9–11]. Despite this, less than a third of people with osteoporotic VFs come to clinical attention [12] due to a variety of reasons including lack of clear clinical triggers to identify who should have diagnostic spinal radiographs.

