We previously carried out a cross-sectional study of 509 older women from primary care, identifying four clinical triggers that could be combined in a simple tool to determine who should have spinal radiographs to identify undiagnosed osteoporotic VFs: height loss, back pain, previous fracture as an adult and rib-to-pelvis distance [13]. A cutoff from the regression equation was subsequently selected which identified all women with more than one VF and half of those with one VF. A large randomised controlled trial (RCT) of this screening tool, Cohort for skeletal health in Bristol and Avon (COSHIBA), was then undertaken in a primary care population of unselected women aged over 65 years [14]; 3200 women were recruited. Allocation to the screening arm approximately doubled the prescription of osteoporosis medications at 6 months follow-up. However, preliminary cost-effectiveness modelling suggested a cost-per-QALY of £30,000, making it unlikely that this would be cost-effective from the National Health Service (NHS) perspective in this setting, in the UK. This was mainly because of a low prevalence of VFs in this unselected population. A key finding from the National Osteoporosis Society into the realities of life with osteoporosis was that 58% of people with VFs have long-term back pain [15]. Therefore, we carried out a case-control study to look more specifically at the population of women aged over 60 years with back pain [16] to identify self-reported characteristics of pain that might help predict who has osteoporotic VFs. This study identified novel independent predictors of VF including shorter duration of back pain, pain described as crushing, pain improving on lying down and pain not spreading down the legs. Area under the curve (AUC) statistics for the combination of these factors to identify women with VFs was 0.85 (95%CI 0.79 to 0.92). Therefore, self-reported pain descriptives may identify people with back pain who have a vertebral fracture [16–18]. The Vfrac study combines the original COSHIBA screening tool with the newly identified pain descriptors (McGill questionnaire and new qualitative focus group work). Only women over 65 years with self-reported back pain will be eligible for this study. The aim of Vfrac is to produce and evaluate an improved screening tool (Vfrac) for use in older people presenting to primary care with back pain.

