### The need for this study

The National Institute for Health and Care Excellence (NICE) guidelines CG146 [19] state the requirement for a study based in primary care to assess which people are at high risk of fracture. The Arthritis Research UK metabolic bone disease musculoskeletal trauma clinical studies group strategy suggested studies of new methods of detection of vertebral fractures and their effects on quality of life as one of their five focuses [20]. Furthermore, patients with osteoporosis and fracture identified earlier identification of osteoporosis as a top 2 research priority in a UK study of 1188 patients [21].

If Vfrac is deemed to be cost-effective, national implementation of Vfrac in primary care and local Fracture Liaison Services is likely to identify more of the currently undiagnosed older women with osteoporotic VFs, who have one of the highest risks of future fracture [22, 23], and will allow reduction in future fracture risk by approximately 50% after intervention [24].

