## Data collection and analysis

Data collection will occur at baseline via self-report, a physical examination at a research clinic and spinal radiograph, and at follow-up via self-report and through GP electronic records.

The items in the questionnaires were chosen based on literature review and previously published work [13, 14, 16]. The questionnaires will contain the following items:Margolis pain diagrams [25] at baselinePHQ-9 [26] at baseline and follow-upPainDETECT [27] at baselineFRAX [28] clinical risk factors only at baselineQ-Fracture [29] at baselineDiagnosis of osteoporosis at baseline and follow-up (‘have you ever been diagnosed with osteoporosis (brittle bones)?’; ‘approximate date of diagnosis’)Traditional risk factors of osteoporosis at baselineEQ5D-5L [30] at baseline and follow-upICECAP-O [31] at baseline and follow-upItems based on focus group work with patients with VFs and based on the McGill Pain questionnaire [16, 18] at baselineDescriptions of pain deemed important during focus group work (REC reference number16/NS/0110) at baselineUse of pain medication at baseline and follow-upCurrent prescription drugs and over the counter medication/remedies/supplements at baseline and follow-upUse of healthcare services at baseline and follow-upWhether results of the radiograph were communicated to the patient at follow-up

During the research clinic, the following information will be collected: height (stand-alone stadiometer), weight, chest expansion, rib-to-pelvis distance, wall-tragus distance and waist circumference. To calculate height loss, we will be relying on the participant to know how tall they were at 25 years. In the baseline questionnaire, the participants are asked ‘how tall were you at aged 25?’ and ‘how tall are you now?’. These data were chosen based on literature review and previous published research [13, 14, 16]. The Vfrac study chief investigator will have access to all spinal radiographs with the study ID number as the only identifying feature.

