### Objectives and outcome measures

(1) To develop a clinical screening tool for identifying older women with back pain who are likely to have VFs. The output of this aim is a simple clinical checklist likely to consist of self-reported data and data from physical examination. The primary evaluative measure will be the accuracy of the Vfrac tool as represented by the sensitivity and specificity. The aim is for sensitivity and specificity of > 80% to justify subsequent evaluation in a definitive trial. Data from the baseline questionnaire, the physical examination and spinal radiograph will be used.

(2) To produce an online version of the combined predictors for easy use as a clinical tool (Vfrac) to identify which older women with back pain are likely to have a VF and, therefore, needs a radiograph. The output of this aim is a web-based online version of the clinical checklist (see primary objective).

(3) To model the cost-effectiveness of Vfrac based on follow-up of the participants to identify if a future definitive cluster randomised controlled trial is appropriate. The output of this aim will be an estimate of likely cost-effectiveness and a list of sources of variation that can be tested in a pilot as part of a future application for funding. Data at follow-up by self-report plus from GP electronic records will be used.

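### Women with an already diagnosed vertebral fracture count as cases while possible consequences of that diagnosis remain candidate predictors, so accuracy can be optimistic for undiagnosed women

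*Protocol article*

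**What the plan says.** **Eligibility.** Study participant selection admits women over 65 with back pain in the last 4 months. It excludes a woman who "has already had a full spinal X-ray in the previous 4 months or considered unsuitable to take part by their GP", and its examples of unsuitability are "cognitive impairment, near end of life or recently bereaved". Recruitment repeats the 4-month film rule and adds being housebound as an example. Neither section mentions a known VF.

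**Purpose.** The need for this study expects that implementation "is likely to identify more of the currently undiagnosed older women with osteoporotic VFs". The formal objective is wider: "To develop a clinical screening tool for identifying older women with back pain who are likely to have VFs".

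**Predictors.** Background and rationale lists the triggers of the earlier tool as "height loss, back pain, previous fracture as an adult and rib-to-pelvis distance" and says that Vfrac combines that tool with pain descriptors. Data collection and analysis adds, among other baseline items, a question on diagnosed osteoporosis, FRAX clinical risk factors, Q-Fracture and current prescription drugs. Analysis—developing the clinical tool links questionnaire and examination data to VF status and takes every likely contender from the univariable step into the multivariable model. It bars no item as a possible consequence of the outcome.

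**Decision rule.** Objectives and outcome measures aims for sensitivity and specificity above 80% to justify a definitive trial.

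**The concern.** A VF diagnosed, say, a year before entry and still visible on the study film is a case in the derivation data. The same diagnosis may have led the woman to report a previous fracture, a diagnosis of osteoporosis or a bone-protective prescription. For previous fracture the link can be an identity: the fracture she reports may be the VF itself. The model can then learn in part that a known VF predicts a VF.

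At stake is how the >80% criterion is read. The benefit described in the rationale, and the new prescriptions counted in the cost-effectiveness section, come mainly from women who do not yet have the diagnosis. If known cases are easier to flag, the cohort could meet the criterion while undiagnosed women fall short of it, and the weights could move from pain descriptors towards diagnosis-related items. The planned bootstrap resamples the same mixed cohort, so it cannot reveal this.

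**Working it through.** **1. The plan's own figure.** Inputs from Sample size: sensitivity 85%, half-width 5 points, 95% confidence, prevalence 12%.

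N = 1.96² × Se(1 − Se) / d² / prevalence = 3.8416 × 0.1275 / 0.0025 / 0.12 ≈ 1632.7, against 1633 stated. The figure reproduces and is not in question. It implies 1633 × 0.12 ≈ 196 VFs.

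**2. What is not in the document.** The article does not give the share f of the cohort's VFs that are already diagnosed. The nearest figure, in Background and rationale, is that "less than a third of people with osteoporotic VFs come to clinical attention". That is an upper bound for people with VFs in general, not for this cohort. I assume f from 10% to 1/3. Sensitivity in known cases (Se_k) is not given either; I assume 90% to 100%.

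**3. Effect on sensitivity.** Whole-cohort sensitivity is a weighted average:

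Se_all = f × Se_k + (1 − f) × Se_u, so Se_u = (Se_all − f × Se_k) / (1 − f), where Se_u is sensitivity in undiagnosed women.

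| f | Se_k | Se_u if Se_all = 80% | Se_u if Se_all = 85% |
|---|---|---|---|
| 10% | 90% | 78.9% | 84.4% |
| 10% | 100% | 77.8% | 83.3% |
| 20% | 95% | 76.3% | 82.5% |
| 1/3 | 90% | 75.0% | 82.5% |
| 1/3 | 95% | 72.5% | 80.0% |
| 1/3 | 100% | 70.0% | 77.5% |

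Example: (0.80 − 1/3 × 1.00) / (2/3) = 0.700. If Se_k = Se_u, then Se_all = Se_u and there is no bias.

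**4. Not every combination changes the decision.** With f = 0.33, Se_k = 95% and Se_u = 72%, Se_all = 0.3135 + 0.4824 = 79.6%, which fails the criterion anyway. With f = 0.25, Se_k = 95% and Se_u = 75%, Se_all = 0.2375 + 0.5625 = 80.0%, which equals the threshold but does not exceed it. With f = 0.33, Se_k = 95% and Se_u = 75%, Se_all = 0.3135 + 0.5025 = 81.6%, which passes overall while undiagnosed women are at 75%.

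**5. Specificity.** It is computed in women with no VF on the study film, so known cases do not enter it. It can move only through the cutoff and the items selected, and in either direction.

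**6. Precision without known cases.** Half-width = 1.96 × √(0.85 × 0.15 / number of VFs), with N = 1633 and 12% prevalence.

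| f | VFs left | Half-width | N needed to keep 5 points |
|---|---|---|---|
| 0 | 196 | 5.0 | 1633 |
| 10% | 176 | 5.3 | 1815 |
| 1/3 | 131 | 6.1 | 2449 |

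At 20% prevalence, the top of the plan's range, 218 to 294 VFs remain and the half-width is 4.1 to 4.7 points.

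**The case against.** The strongest reply is that the plan enrols the population it names. The Abstract, Primary aim, Outline, and Objectives and outcome measures all speak of older women with back pain, without the word undiagnosed. That word appears where the earlier cross-sectional study is described and where later implementation is foreseen. A known old VF also does not exclude a new one. This stands against any claim that these women are ineligible or worthless to the study. It does not remove the mismatch with the rationale, and it does not make a predictor that may contain the outcome harmless.

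Second, osteoporosis diagnosis and prescriptions are collected at baseline and follow-up, which also suits the cost-effectiveness objective, and variables are to be deleted with clinical judgement. This stands in part: their candidate status is implied by the questionnaire list and the modelling rule, not stated. Previous adult fracture does not depend on that inference.

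Third, a candidate list and subgroup reporting may sit in the full protocol or an analysis plan that is not shown. Silence on those alone would be no finding. The point rests on what the article does fix: the eligibility rule, the inherited predictor and the all-contenders rule, set beside its stated purpose.

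A reader might infer that accuracy is overstated as a matter of fact. The document does not support that, because the share of known cases and the predictors that survive selection are both unknown. A reader might also infer that the cost-effectiveness model is invalid. That goes too far: the model counts new prescriptions after the radiograph and uses expert opinion on care without Vfrac, so it deals with the issue at least in part.

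**Conclusion.** The point holds as a conditional risk. Women with a VF diagnosed before the 4-month window are eligible and count as cases, and at least one candidate predictor can be the same event under another name. Sensitivity, AUC and the cutoff can therefore be optimistic for undiagnosed women.

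Under the assumed ranges, a sensitivity that just reaches 80% overall is about 1 to 10 points lower in undiagnosed women. At 85% overall it is 77.5% to 84.4%, so most of the assumed range still clears 80%. These sizes rest on my assumptions for f and Se_k, not on trial data. Neither the target of 1633 nor the eligibility rule is wrong in itself. Restricting derivation to undiagnosed women, or barring predictors outright, is debatable. Separating the two groups in the reporting is a cheap and worthwhile improvement.

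**What to change.** - Add a prior-VF item with date to the baseline questionnaire and to the GP record extraction. The extraction described under Outline does not name prior VF. It takes place 3 months after a film whose report goes to the GP, so only entries dated before the study radiograph should count.
- Within previous fracture, record spinal and non-spinal fractures separately, so that the predictor does not contain the outcome.
- Report sensitivity, specificity and AUC with and without women whose VF was known before the study radiograph, and check the >80% criterion in those without.
- As a sensitivity analysis, refit the model without diagnosis-driven items (osteoporosis diagnosis, anti-osteoporosis drugs, spinal fracture history).

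The cost is one dated data item and some loss of precision in the restricted group: about 5.3 to 6.1 points instead of 5.0 at 12% prevalence and 85% sensitivity. No change in enrolment is needed. Holding 5 points in that group would take about 1815 to 2449 women, which I do not ask for.

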### Sample size

The sample size is based on the following assumptions:A prevalence of VFs between 12 and 20%, based on data from the European Vertebral Osteoporosis Study (EVOS) [12]. This is based on the general population of women under 65 years and is, therefore, likely to be lower than the true prevalence of VFs in older women with back pain.A margin of error (that is, the half-width in 95% confidence intervals of sensitivity or specificity) of 5%.Sensitivity and specificity of the Vfrac tool between 80 and 95%.

Table 2 shows the range of sample sizes according to prevalence of VFs and sensitivity or specificity of the Vfrac tool; we will aim for a sample size of 1633. This sample size will be large enough to encompass any specificity of Vfrac as sample sizes required for specificity are much lower.

**Table 2 Tab2:** Calculation showing range of sample sizes according to prevalence of vertebral fractures and sensitivity (A) or specificity (B) of the Vfrac tool

	Prevalence of vertebral fractures		
	12%	15%	20%
Sensitivity			
80%	2050	1640	1230
85%	1633	1306	980
90%	1159	927	695
95%	609	487	365
Specificity			
280	289	308	80%
232	231	245	85%
158	164	174	90%
83	86	92	95%

### Recruitment

Recruitment will be from the community via primary care. Women over 65 years who can give informed consent and are not found to be unsuitable for the study by their GP (e.g. are not housebound) will be sent study invitation packs. The invitation pack will contain an invitation letter signed by the potential participant’s GP, the participant information sheet, two copies of the first consent form and the baseline questionnaire. The invitation packs will be sent to the potential participants by their own general practitioner. The invitation pack will make it clear that the study wishes to include women over 65 years who have had back pain in the previous 4 months, even if they have had back pain for more than 4 months. Reminder letters will be sent after 4–6 weeks if no response is initially received.

Participants willing to participate will be asked to complete the baseline questionnaire and one copy of the consent form, returning these to the researchers using a prepaid envelope. The consent form will contain a section for the participant to supply us with their title, name, address, phone number, email address and contact preferences.

Upon receipt, the completed consent form and baseline questionnaire will be checked by a study researcher. The first question in the baseline questionnaire is a screening question: ‘have you had back pain in the previous 4 months?’. If the participant has answered ‘no’, then they are not eligible for the study and will be sent a thank you letter. If a potential participant is eligible, they will be booked in for a physical examination and spinal radiographs. A research administrator will phone the participant to make the appointment after ensuring the participant is willing to continue taking part in the study and has not had a full spinal radiograph in the previous 4 months. Participants will be asked to give written face-to-face consent for the physical examination and the radiographs at the research clinic.

Each participant has the right to withdraw from the study at any time. If any participant loses capacity during the study, they will be withdrawn but their data to date kept.

### Follow-up

Follow-up will occur 3 months after the spinal radiograph via post and through data collection from GP electronic records. The participants will receive a follow-up questionnaire and cover letter. If there is no reply after 2–3 weeks, the participant will receive another follow-up questionnaire and reminder cover letter.

## Data collection and analysis

Data collection will occur at baseline via self-report, a physical examination at a research clinic and spinal radiograph, and at follow-up via self-report and through GP electronic records.

The items in the questionnaires were chosen based on literature review and previously published work [13, 14, 16]. The questionnaires will contain the following items:Margolis pain diagrams [25] at baselinePHQ-9 [26] at baseline and follow-upPainDETECT [27] at baselineFRAX [28] clinical risk factors only at baselineQ-Fracture [29] at baselineDiagnosis of osteoporosis at baseline and follow-up (‘have you ever been diagnosed with osteoporosis (brittle bones)?’; ‘approximate date of diagnosis’)Traditional risk factors of osteoporosis at baselineEQ5D-5L [30] at baseline and follow-upICECAP-O [31] at baseline and follow-upItems based on focus group work with patients with VFs and based on the McGill Pain questionnaire [16, 18] at baselineDescriptions of pain deemed important during focus group work (REC reference number16/NS/0110) at baselineUse of pain medication at baseline and follow-upCurrent prescription drugs and over the counter medication/remedies/supplements at baseline and follow-upUse of healthcare services at baseline and follow-upWhether results of the radiograph were communicated to the patient at follow-up

During the research clinic, the following information will be collected: height (stand-alone stadiometer), weight, chest expansion, rib-to-pelvis distance, wall-tragus distance and waist circumference. To calculate height loss, we will be relying on the participant to know how tall they were at 25 years. In the baseline questionnaire, the participants are asked ‘how tall were you at aged 25?’ and ‘how tall are you now?’. These data were chosen based on literature review and previous published research [13, 14, 16]. The Vfrac study chief investigator will have access to all spinal radiographs with the study ID number as the only identifying feature.

